### Sample size and sampling

#### Community quantitative surveys

For the community series of cross sectional surveys, we adopt the formula by Hemming et al. 2016 for cross sectional sample size determination for a stepped wedge study. To determine a moderate effect size of 0.3 (SD 1) for say change in Blood pressure at 5% significance, and detectable power of 88%, before and after the exposure to the intervention, given a sample size that is feasible and realistic in these setting, with four (4) steps and five (5) clusters per step, a total sample size of 50 participants per cluster is assumed reasonable [27]. However, assuming an intracluster correlation coefficient, r, of 0.01, a fixed cluster sample size, m = 50, survey rounds, t = 5 and a design effect of 2.93 [27] with 20 predetermined clusters; the required total sample size per survey round is 2930 households. We recognise that a random sample of household in a vast geographic setting can return a lot of non-responses. Thus, to cater for non-responding households and to avoid replacement of randomly selected eligible households, we factor in a non-response of 30% and generate the final household sample of 4000; with each cluster contributing 200 households. *Sampling households and participants*: The sampling frame for the surveys is generated through a mapping and listing exercise. All households in the catchment area are assigned a unique number to generate a sampling frame. A random sample of 200 eligible households with at least one adult per household is generated from the sampling frame using a random number generator. The selection is conducted by the study statistician. Study personnel (trained research assistants) approach the selected households for recruitment into the household/community survey. When a selected household is approached and has at least one eligible adult, study personnel describe the purpose of the study in the appropriate language, obtain participant consent and administer the study questionnaire and conduct anthropometric and blood pressure measurements using standardised and validated equipment. All eligible adults in the household aged 25–70 years are enrolled.

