
Paired t-tests will be run to compare means across clusters and within clusters. However, given the time trend and clustering effects, we proceed to adjust for different observation periods and for clustering in the data by fitting an appropriate generalised linear mixed model or using generalised estimating equations. For continuous (and normally distributed) outcomes, we fit a linear model with random effect for cluster and fixed effect for each step; and, for binary outcomes, a logistic regression model with random effect for cluster and fixed effect for each step.

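### The stated community-survey model has a random effect for cluster only, so its standard errors are too small whenever adults in a household are correlated or within-parish correlation falls between rounds

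*Protocol article*

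**What the plan says.** Data analysis first promises to adjust for period and clustering by "fitting an appropriate generalised linear mixed model or using generalised estimating equations". It then names the model for continuous outcomes: "we fit a linear model with random effect for cluster and fixed effect for each step". Binary outcomes get a logistic model with the same two ingredients. The article states no household term, no cluster-by-round term and no robust variance.

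The sampling is described under Community quantitative surveys. Households are drawn at random, 200 per cluster, and "All eligible adults in the household aged 25–70 years are enrolled". The Evaluation plan has cross-sectional surveys at months 0, 6, 12, 18 and 24. The sample size paragraph works "with four (4) steps and five (5) clusters per step", so 20 clusters, and uses a single correlation, "assuming an intracluster correlation coefficient, r, of 0.01". It gives no household correlation, no number of adults per household and no correlation between rounds.

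Effectiveness is listed as the secondary outcome. Implementation is primary.

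**The concern.** In a stepped wedge, much of the information on the intervention effect comes from comparing rounds within a cluster. What matters is therefore how variable a parish-by-round mean is. Two features of this survey can add to that variability, and a constant cluster intercept absorbs neither.

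- **Household.** Adults in one home tend to resemble each other in blood pressure, diet and smoking. Enrolling all of them gives less information than the same number of unrelated adults.
- **Round.** A single cluster intercept assumes that two people in a parish are as alike when surveyed 24 months apart as when surveyed in the same round. If correlation falls between rounds, each parish-by-round mean carries an extra shared deviation.

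The model would count both as independent individual noise that averages away over several hundred adults. Confidence intervals would then be too narrow, and a small or null effect on blood pressure, BMI or knowledge could be declared real too often.

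**Working it through.** **Inputs from the article.** 20 clusters, 4 steps of 5, 5 rounds, SD 1, effect 0.3, 5% significance (taken as two-sided), ICC 0.01. Households per cluster-round: 2930/20 = 146.5, about 147. The alternative, 200 × 0.7 = 140 responding, changes little.

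**Assumed, because the article does not give them.** Adults per household a = 1 or 2; household correlation h = 0 to 0.3; cluster autocorrelation c = 0.8 to 1. Here c is the between-round correlation divided by the within-round correlation, and c = 1 means no fall.

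**Step 1: the article's own power.** With one random cluster effect (variance τ²) and cell-mean error variance s², this design gives

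Var = 20·s²·(s² + 5τ²) / (250·s² + 750·τ²).

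The constants follow from the layout: U = 50, W = 750, V = 150, so 20U − W = 250 and U² + 100U − 5W − 20V = 750. With 10 people per cluster-round, s² = 0.99/10 = 0.099 and τ² = 0.01. Var = 0.29502/32.25 = 0.00915, SE = 0.0956, and power = Φ(0.3/0.0956 − 1.96) = 88.0%. That matches "at 5% significance, and detectable power of 88"%, provided the 50 per cluster is the total over five rounds. With 50 per cluster-round, SE = 0.0471 and power is above 99.9%.

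**Step 2: true against reported standard error.** With n households per cluster-round, the true covariance of parish-by-round means has

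- a constant part, 0.01·c;
- a round-specific part, 0.01·(1 − c) + 0.99·[1 + (a − 1)h]/(n·a).

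The cluster-only fit instead uses a residual variance of about 0.99 divided by n·a. The true SE is the sandwich SE of that same estimator under the true covariance. Actual test level = 2Φ(−1.96 × model SE / true SE).

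**Worked case** (n = 147, a = 2, h = 0.2, c = 0.8). The cell-mean variance has three parts: individual 0.99/294 = 0.0034, household excess 0.99 × 0.2/294 = 0.0007, cluster-by-round 0.0020. The cluster-only fit settles at τ² = 0.00853 and s² = 0.99147/294 = 0.00337, so Var = 0.003104/7.241 = 0.000429 and the model SE is 0.0207. The true SE is 0.0274. Then 1.96 × 0.0207/0.0274 = 1.48, and 2Φ(−1.48) = 13.9%.

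**Results at n = 147, ICC 0.01:**

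| Adults per household | Household correlation | Autocorrelation | Model SE | True SE | Actual level |
|---|---|---|---|---|---|
| 2 | 0 | 1 | 0.0208 | 0.0208 | 5.0% |
| 2 | 0.1 | 1 | 0.0208 | 0.0217 | 6.1% |
| 2 | 0.2 | 1 | 0.0208 | 0.0227 | 7.3% |
| 2 | 0.3 | 1 | 0.0208 | 0.0236 | 8.4% |
| 1 | – | 0.95 | 0.0288 | 0.0298 | 5.8% |
| 1 | – | 0.8 | 0.0287 | 0.0323 | 8.2% |
| 2 | 0.2 | 0.8 | 0.0207 | 0.0274 | 13.9% |

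**Step 3: check by simulation.** REML fits of the cluster-only model to individual data (140 households, 2 adults, 2000 runs each) rejected 5.0% with neither component, 8.3% with h = 0.2, 11.0% with c = 0.8 and 13.7% with both. The formula at 140 households gives 5.0%, 7.3%, 11.4% and 13.6%.

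**Step 4: cost of the right model.** In the worked case, put s² = 0.0020 + 0.99 × 1.2/294 = 0.00604 and τ² = 0.008 into Step 1. Var = 0.00556/7.510 = 0.000741 and SE = 0.0272. For 0.3 SD, 0.3/0.0272 = 11.0, so power is above 99.9%.

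**The case against.** The best defence is that the size is not in the documents. Household correlation, adults per household and autocorrelation are all assumed here, and mild values do mild harm: 5.8% at autocorrelation 0.95, 6.1% at household correlation 0.1. The outcomes are secondary, the article calls its core analyses qualitative, and an effect of 0.3 SD would be detected under either model. All of that stands, and it limits the point to small or null effects. It does not remove the point, because the random structure is written down and does not match the enrolment rule in the same article.

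A reader might infer more than the documents support:

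- **Error rates near 34%.** That needs an ICC of 0.05, five times the article's figure.
- **Surveying the same parishes repeatedly is itself the fault.** A cluster intercept handles correlation that is constant over rounds. Only a fall between rounds does harm.
- **The omitted components dominate the variance.** In the worked case they come to 0.0027 against 0.0034 for individual sampling.
- **The large survey drives the inflation.** This holds for the round component: with autocorrelation 0.8 and one adult, 5.1% at 10 per cluster-round, 6.0% at 50 and 8.2% at 147. The household part stays at about 7% (correlation 0.2, two adults) at 10, 147 or 300 households.
- **The GEE route is invalid, or the intervention term was forgotten.** The article names no GEE variance estimator. Its analysis by randomised crossover time shows that exposure is meant to be in the model. Both are condensed wording, not errors.
- **Every effectiveness outcome is affected alike.** Household enrolment does not apply to the facility patient survey.

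**Conclusion.** The point holds for the community-survey effectiveness outcomes. Followed as written, the model reports standard errors that are too small unless household correlation is zero and between-round correlation equals within-round correlation. Confidence in that direction is high.

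Confidence in the size is moderate. At the article's ICC and about 147 households per cluster-round, the actual level of a 5% test is roughly 6% to 8% with one component present at the tabulated values, and about 14% with household correlation 0.2, autocorrelation 0.8 and two adults. Power is not threatened. This should be corrected before analysis, but it does not undermine the design.

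**What to change.** For the community survey, state the model with fixed effects for round and for intervention, and random effects for cluster, cluster-by-round and household. Give the logistic model the same random effects. For the linear model, use Kenward-Roger or Satterthwaite inference. If GEE is used instead, specify a cluster-level sandwich variance with a small-sample correction for 20 clusters; an uncorrected one rejected about 8% in simulation. For the facility patient survey, only the cluster-by-round term needs adding.

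The cost is a short change to the analysis text, provided household and round identifiers are kept in the data set, and wider intervals. These widen by about 9% with household correlation 0.2 alone (0.0227/0.0208) and about 31% in the worked case (0.0272/0.0207). Enrolment need not change. Taking one adult per household would alter recruitment after the baseline survey had begun, and the cluster-by-round term would still be needed.

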### Evaluation plan

To evaluate the study, we propose to conduct a series of cross-sectional surveys every 6 months at time (T) 0, T6, T12, T18 and T24 at the community and health facility levels. We assess with key community and household members, health facilities, health workers, and patients. The evaluations uses both: qualitative assessments – to evaluate the process, barriers and opportunities; and quantitative measurements – to assess effects and process outcomes. During the interventions, formative processes (process evaluations) and detailed documentation of process, costs and activities take place.

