### Data analysis

Qualitative data will be analysed using the framework analysis technique, which facilitates thematic analysis.

The quantitative analyses will be guided by the principle of intention-to-treat and clusters analysed according to their randomised crossover time irrespective of whether crossover was achieved at the desired time. The analysis will be conducted in Stata or R Software. Initially, descriptive analysis (before and after) will be conducted and categorical data presented using counts and percentages, while continuous variables presented using measures of central tendencies. No multiple imputations will be conducted for missing data. The following descriptive are envisioned.Reach of the project, captured through: the number and percentage of providers and individuals enrolled into the project at the community and health facility levels; the number of individuals partaking and adhering to the recommended interventions at the various levels.Effectiveness: Activities and clinical endpoints will be used to assess effectiveness of the project at selected intervals observed longitudinally. The measures include: the proportion of project activities (community/health facilities) achieved at any point in time; change in clinical profiles e.g. blood pressures, BMI, alcohol history, smoking status, quality of life etc., achieved at 0, 6, 12, 18 and 24 months; and proportion of completers and attritors.Adoption: The number/percentages of individuals/providers approached or agreed to take part in the intervention (s) and proportion of individual providers (CHW, Peers or NPHW) that deliver the intervention.**I**mplementation: Captured by detailed description of the contextual adaptations of the project, the time required for intervention, and the costs of the intervention. Implementation information including process, facilitators and barriers, costs, and contextual issues will be analysed descriptively and qualitatively. Readiness of implementation (Available resources) – BP monitoring devices, Weighing scales, Stadiometers, measuring tapes, Glucometers and strips, first line antihypertensive drugs, guidelines, personnel, space, time etc. will be descriptively described and presented using graphs. Quality and quantity of equipment and their functionality, supplies and other necessary infrastructure will be descriptively analysed. Fidelity – Evidence of use of guidelines and protocols/simplified algorithm and any iterations recorded will be analysed descriptively and qualitatively. Costs - Costs associated with implementing the packages. Monetary requirements for each intervention (community and health facility based) will be analysed descriptively as a measure of sustainability based on feedback reports from community members, patients, CHWs, health unit staff and project and field coordinators.Maintain: The extent to which the project becomes part of routine practice and policy will be explored. Evaluation of maintenance will include the following: Analysing the proportion of health providers who are introduced to the enhanced approach and those adapting the strategies.

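### The survey outcome models name only cluster and step terms; age and sex should be prespecified, because the respondent mix could shift with exposure and adjustment is nearly free

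*Protocol article*

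**What the plan says.** The Data analysis section of the Protocol article proposes to allow for observation period and for clustering by "fitting an appropriate generalised linear mixed model or using generalised estimating equations". It then names terms by outcome type. For continuous outcomes, "we fit a linear model with random effect for cluster and fixed effect for each step". For binary outcomes, "a logistic regression model with random effect for cluster and fixed effect for each step". Neither sentence names age, sex or any other individual-level covariate, and neither rules one out.

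The Evaluation plan describes "a series of cross-sectional surveys every 6 months at time (T) 0, T6, T12, T18 and T24". Under Community quantitative surveys, "A random sample of 200 eligible households with at least one adult per household is generated from the sampling frame"; every eligible adult aged 25–70 in a selected household is enrolled, and non-responding households are not replaced. Instead, "we factor in a non-response of 30% and generate the final household sample of 4000".

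One phrase points the other way on the type of sample. Among the effectiveness measures, Data analysis lists the "proportion of completers and attritors", which is language for a followed cohort and not for fresh cross-sections.

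**The concern.** In a stepped wedge with repeated cross-sections, randomisation acts on the time at which a cluster crosses over. It does not act on who answers the door afterwards. Respondents in exposed periods are recruited after crossover, and the Community plan has community health workers beginning home visits, screening and motivational interviewing at that point. Contact of that kind could change who is at home or willing to take part. Oversampling for non-response restores the number of respondents but not their composition.

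Blood pressure, BMI, waist-hip ratio, smoking and alcohol use can all be expected to vary with age and sex. If exposed respondents are systematically older or younger, or differ in sex mix, a model with cluster, step and exposure terms attributes the resulting difference to the programme. A larger sample does not reduce that error. It narrows the interval around it. Apart from bias, leaving out prognostic covariates gives away some precision on continuous outcomes.

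**Working it through.** **Inputs from the Protocol article (Community quantitative surveys).** 20 clusters, 4 steps of 5 clusters, 5 rounds, intracluster correlation 0.01, target effect 0.3 SD, 5% significance (two-sided assumed), stated power 88%, 50 participants per cluster in total, 200 households per cluster per round, 30% non-response.

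**Assumptions, not in the documents.** Age and sex explain 10–20% of individual variance. The outcome rises 0.015–0.03 SD per year of age. Exposed respondents differ by 1–2 years in mean age. There is one respondent per responding household, so 200 × 0.7 = 140 per cluster-round. The model includes an exposure term.

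**Formula.** For a model with a cluster random effect, fixed round effects and an exposure term,

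Var = I·s²(s² + T·τ²) / [(I·U − W)s² + (U² + I·T·U − T·W − I·V)τ²]

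with I = 20, T = 5, τ² = 0.01 and s² = 0.99/m, where m is the number per cluster-round. U, the number of exposed cluster-rounds, is 50. W, the sum over rounds of squared exposed counts, is 0 + 25 + 100 + 225 + 400 = 750. V, the sum over clusters of squared exposed rounds, is 5(16 + 9 + 4 + 1) = 150. Hence I·U − W = 250, and the multiplier of τ² is 2500 + 5000 − 3750 − 3000 = 750.

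**The plan's own figure.** Take m = 50/5 = 10, so s² = 0.099. Var = 0.29502/(24.75 + 7.5) = 0.00915 and SE = 0.0956. Power = Φ(0.3/0.0956 − 1.96) = 88.0%. The stated 88% reproduces, and it was obtained without covariates.

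**Precision at 140 per cluster-round.** s² = 0.00707; Var = 0.0080715/(1.7679 + 7.5) = 0.000871; SE = 0.0295 SD. Multiplying s² by 1 − R² gives:

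| R² (assumed) | SE | Variance reduction | Variance reduction, cluster autocorrelation 0.8 |
|---|---|---|---|
| 0 | 0.0295 | – | – |
| 0.10 | 0.0281 | 9% | 7% |
| 0.20 | 0.0266 | 19% | 14% |

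Power for 0.3 SD is above 99.9% in every row.

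**Which shifts bias the estimate.** Fitting the same model by generalised least squares to fixed shifts in cluster-round means (146.5 per cluster-round, that is 2930/20) gives:

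| Shift in respondent mix | Effect on the estimate |
|---|---|
| Common to all clusters in a round | 0 |
| Random by cluster and round | mean 0; adds noise only |
| 0.10 SD, from crossover onwards | 0.100 SD |
| 0.10 SD, first exposed round only | 0.093 SD |

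**What an exposure-linked shift would do.** A 2-year difference at 0.015–0.03 SD per year is 0.03–0.06 SD, or 10–20% of the 0.3 SD target. Against an SE of 0.0295 that is 1.0–2.0 standard errors. The chance of |Z| > 1.96 when the programme does nothing rises from 5% to 17–53% (15–45% with cluster autocorrelation 0.8). A 1-year difference gives about 8–17%. These figures depend wholly on the assumed shift; with no shift the rate stays at 5%.

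**The case against.** The strongest reply is that this is a condensed article and covariate lists are commonly left to a full protocol or analysis plan. The model sentence, read literally, does not even contain an intervention term, so it is plainly shorthand for how period and clustering are handled. A reader might infer that the models are stated in full and that age and sex have been deliberately excluded; the text does not support that. What remains is that the article does name what it adjusts for and does give terms for each outcome type. Age and sex adjustment is a concrete improvement on that published model, and adding it after the data are seen would look post hoc.

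A reader might also infer that the effect estimate will be biased. The documents do not support this. Households are drawn at random by the study statistician and approached by trained research assistants. The 30% is an allowance for a large area and is not linked to exposure, and no section says that response changes at crossover. This part of the objection stands, so the concern is a risk only.

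Nor does the sentence "No multiple imputations will be conducted for missing data" strengthen the case. Imputation deals with missing items, and a household that never responds supplies no record to impute from.

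Two further points stand. The precision gain does not alter the stated power. And fresh samples at each round are inferred from the cross-sectional wording; the article never says that households are redrawn, and its reference to completers and attritors conflicts with that reading.

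**Conclusion.** The point holds as a recommended improvement to the stated analysis of secondary (effectiveness) outcomes. The models as published carry no protection against a change in respondents' age and sex mix that coincides with exposure, and such a change would enter the estimate almost one for one. Whether it will occur cannot be judged from the documents. The more certain gain is a variance about 9–19% lower for continuous outcomes, or 7–14% with cluster autocorrelation 0.8, if age and sex explain 10–20% of variance. That range is an assumption, as are the age shift and slope behind the false-positive figures, and the calculation ignores correlation between adults in the same household. Adjustment removes only the age- and sex-related part of any exposure-linked selection.

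**What to change.** In Data analysis, state that the linear and logistic models for the survey effectiveness outcomes include the exposure indicator, the cluster random effect, the step fixed effects, and age (spline or bands) and sex as fixed effects, and that this is the main analysis. Report the model without age and sex as a sensitivity analysis. For binary outcomes, also report an age-sex standardised difference in proportions, because the adjusted and unadjusted odds ratios do not estimate the same quantity. In the same revision, say whether households are redrawn each round, and reconcile the reference to completers and attritors with the cross-sectional design.

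The cost is a sentence or two, a few degrees of freedom and one standardisation step for binary outcomes. No extra participants are needed. Age has to be known to apply the age limits, and sex is almost certainly recorded, although the article does not say so.
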